## Objectives

The aim of this study is to design and conduct a double-blind, randomized, placebo-controlled trial, to evaluate the efficacy and safety of Qingpeng ointment for AGA. The primary objective is to evaluate the efficacy of Qingpeng ointment in relieving the joint pain and reducing the joint swelling of patients with AGA. The secondary objectives are to evaluate the efficacy of Qingpeng ointment in improving the joint mobility and relieving the joint redness in patients with AGA, and to evaluate the safety of Qingpeng ointment.

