### Outcomes

#### Primary outcomes

Because the objective of this study is to investigate the efficacy of Qingpeng ointment for relieving pain and swelling of joints in patients with AGA, changes in joint pain severity (measured using VAS), joint swelling degree (measured using VAS), and width and thickness of affected joints (measured using vernier calipers) between baseline and treatment completion will be considered as the primary outcomes.Joint pain: Degree of joint pain will be measured by participants, using a visual analogue scale (VAS, 0–10 points, 0=no pain, 10=intolerable pain), at baseline, every day during treatment, and after 7-day treatment.Joint swelling:2.1 The width and thickness of each affected joint will be measured using vernier calipers (brand: Ruineng, model: NR0139) at baseline, every day during treatment, and after 7-day treatment.2.2 Degree of joint swelling will be measured by participants, using a visual analogue scale (VAS, 0–10 points, 0=no swelling, 10=intolerable swelling), at baseline, every day during treatment, and after 7-day treatment.

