### Sample size estimation

This study includes two primary outcomes: joint pain and joint swelling. Sample size was estimated based on these two primary outcome measures. Estimation according to joint pain was based on results from a previous study [23]. In this study, 47% participants in treatment group (Qingpeng ointment plus diclofenac sodium tablets) had significant relief of joint pain (the score of joint pain degree measured by a self-developed scale reduced by 6 points), and 25% participants in control group (diclofenac sodium tablets) had significant relief of joint pain. On the basis of a 5% type I error rate (*α*=0.05) and a power of 90% (*β*=0.1), the sample size of each group was 82. Assuming a 20% dropout rate, a total of 206 participants should be recruited, with 103 participants in each group.

Estimation according to joint swelling was likewise based on results from another previous study [19], which established score of joint swelling measured by a 0–3 points scale as 0.45 points after receiving Qingpeng ointment plus etoricoxib tablets, and the estimated standard deviation is 0.37. Score of joint swelling after receiving vaseline plus etoricoxib tablets is 0.87, and the estimated standard deviation is 0.64. On the basis of a 5% type I error rate (*α*=0.05) and a power of 90% (*β*=0.1), the sample size of each group was 27. Assuming a 20% dropout rate, a total of 68 participants should be recruited, with 34 participants in each group.

Based on these results, we chose the larger sample size of 206 participants, with 103 participants in each group.

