### Statistical analysis

Statistical analysis will be performed using SAS 9.2 software, with a statistical significance of *p* value less than 0.05. Normally distributed continuous variables will be described using mean ± standard deviation (SD), and non-normally distributed continuous variables will be described using median and interquartile range (IQR). Categorical variables will be described using frequencies and percentages. Primary outcomes will be analyzed according to the intention-to-treat principle. Intra-group differences of continuous variables will be tested for significance using paired-samples *t* test when the data is normally distributed, and will be tested using non-parametric test when the data is non-normally distributed. Between-group differences of continuous variables will be tested for significance using independent-samples *t* test when the data of the two groups are normally distributed and have equal variance, and will be tested using non-parametric test when the data of the two groups are non-normally distributed or have unequal variances. Chi-square test will be used for categorical data. Data from participants who drop out from this study will be implemented by the last-observation-carried-forward (LOCF) method. Interim analyses will not be performed. For the co-primary endpoints, Bonferroni correction will be performed to correct multiplicity.

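### Single-step Bonferroni on the primary endpoints gives up about 4 to 8 points of pain power that Holm's test would keep at the same family-wise error, and the article does not say whether one or both endpoints must succeed

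*Protocol article*

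**What the plan says.** The multiplicity rule is one sentence in Statistical analysis: "For the co-primary endpoints, Bonferroni correction will be performed to correct multiplicity". It gives no divisor and no rule for declaring the trial positive. The general significance criterion in the same section is "with a statistical significance of *p* value less than 0.05", with no statement of one- or two-sided testing.

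The Objectives section puts both symptoms into a single aim: "The primary objective is to evaluate the efficacy of Qingpeng ointment in relieving the joint pain and reducing the joint swelling". Sample size estimation counts two endpoints, "This study includes two primary outcomes: joint pain and joint swelling", and sizes each one separately "On the basis of a 5% type I error rate" with 90% power. The Primary outcomes section lists more variables. Besides pain on a VAS it names "joint swelling degree (measured using VAS), and width and thickness of affected joints (measured using vernier calipers) between baseline and treatment completion", which makes three or four variables depending on whether width and thickness count separately.

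**The concern.** Two things are at stake.

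The first is efficiency. Bonferroni for two endpoints holds each at 0.025 whatever the other one shows. Holm compares the smaller p value with 0.025 and, once that is rejected, the larger with 0.05. It needs no assumption about the correlation between endpoints. On the planning inputs pain sets the sample size and swelling has power to spare, so the cost of staying at 0.025 falls almost wholly on pain.

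The second is interpretation. A Bonferroni correction suits a trial in which either endpoint can carry a claim. The co-primary label and the joined objective could be taken to mean that both must succeed, in which case each is tested at full alpha with no correction. The article does not settle which applies. With swelling p = 0.001 and pain p = 0.20, the first rule gives a positive trial and the second a negative one.

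**Working it through.** **Inputs, all from Sample size estimation.** Pain responders: "47% participants in treatment group" against 25% under control. Swelling: mean 0.45 (SD 0.37) against 0.87 (SD 0.64). Alpha 0.05, power 90%. Evaluable per group: 82 for pain and 27 for swelling. With 20% dropout these become 103 and 34.

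**Reproducing the stated sizes.** For pain, with mean proportion 0.36 and difference 0.22, use n = 2 × 0.36 × 0.64 × (z_α + z_β)² / 0.22².
- One-sided: (1.645 + 1.282)² gives 81.5, so 82, as stated.
- Two-sided: 100.04, so 101. Other two-sided formulas give 95 to 107.

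For swelling, n = (0.37² + 0.64²) × (z_α + z_β)² / 0.42².
- One-sided: 26.5, so 27, as stated.
- Two-sided: 32.6, so 33.

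Dropout: 82/0.8 gives 103 and 27/0.8 gives 34. The stated sizes therefore match a one-sided 5% test without a Bonferroni split. Because the article does not state sidedness, both versions follow.

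**Pain power under Bonferroni for two (0.025) and at 0.05.** Power = Φ[(0.22 − z_α·s0)/s1], with s0 = √(2 × 0.36 × 0.64/n) and s1 = √((0.47 × 0.53 + 0.25 × 0.75)/n). At n = 82, s0 = 0.0750 and s1 = 0.0730. Two-sided at 0.05: (0.22 − 1.960 × 0.0750)/0.0730 = 1.00, so 84.2%. Two-sided at 0.025: (0.22 − 2.241 × 0.0750)/0.0730 = 0.71, so 76.2%.

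| Per group | Test | At 0.025 | At 0.05 | Difference (points) |
|---|---|---|---|---|
| 82 | two-sided | 76.2% | 84.2% | 8.0 |
| 82 | one-sided | 84.2% | 90.7% | 6.6 |
| 103 | two-sided | 85.9% | 91.4% | 5.5 |
| 103 | one-sided | 91.4% | 95.4% | 4.0 |

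Differences are taken before rounding. With unpooled variance, the first row is 78.0% against 85.4%. The 103 rows apply if last observation carried forward fills every dropout in the intention-to-treat analysis.

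**Why Holm reaches the 0.05 column.** At 82 per group the swelling noncentrality is 0.42/√((0.37² + 0.64²)/82) = 5.145. Swelling power is then 99.8% at two-sided 0.025, so Holm almost always moves on to test pain at 0.05. Holm's pain power matches the 0.05 column to about 0.1 point in every row, for correlations from 0 to 0.7.

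**A larger family.** With four primary variables Bonferroni uses 0.0125. Pain power at 82 per group is then 67.3% two-sided (pooled; about 70% unpooled) or 76.2% one-sided. Holm's recovery depends on the power of the three swelling measures, for which the article gives no inputs. Assuming correlation 0.5 and swelling power from about 80% to over 99%, Holm gives pain about 77% to 85% (unpooled, two-sided), against about 70% for Bonferroni.

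**The success rule.** Uncorrected testing of two independent endpoints at 0.05 has family-wise error 1 − 0.95² = 9.75%. At 0.025 each it is 1 − 0.975² = 4.94%. A correction is therefore needed if either endpoint suffices. If both must succeed at 0.05, power for both at 82 per group is about 84% two-sided or 91% one-sided.

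**The case against.** Bonferroni is valid, prespecified and gives simple simultaneous intervals. A more powerful alternative does not make the stated method an error. That stands: the point is avoidable inefficiency, with no failure of type I error control.

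A reader might infer from the co-primary label and the single objective that both endpoints must succeed, so that the correction is spent for nothing. The text does not support this. The objective, to "evaluate the efficacy of Qingpeng ointment in relieving the joint pain and reducing the joint swelling of patients with AGA", may simply list two aims, the sample size is worked out for each endpoint separately, and the one operative instruction, Bonferroni, fits separate claims. If either endpoint suffices, some correction is required. What remains is that single-step Bonferroni is not the only way to supply it.

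A reader might also take swelling p = 0.001 with pain p = 0.04 as a result that is both a win and a failure. It is a win if either endpoint suffices at 0.025 and a win if both are required at 0.05. It fails only under a third rule, both at 0.025, which the article does not set out. The readings diverge on a case such as pain p = 0.20, and there the choice between Holm and Bonferroni is irrelevant.

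A condensed article may leave the success rule to the full protocol or analysis plan, so its absence alone is a request for clarification. The correction method, by contrast, is fixed in this text.

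The 8-point figure is the largest of the four two-endpoint cases. It needs a two-sided test, 82 per group and a divisor of two, whereas the stated sizes reproduce one-sided.

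**Conclusion.** The point holds as a recommended improvement. With two endpoints, replacing single-step Bonferroni by Holm raises pain power by about 4 to 8 points at no cost in family-wise error, and the stake is larger if the family has three or four members.

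The size rests on assumptions. The pain inputs are a responder proportion on a self-developed scale from an add-on study, while the primary analysis is change in VAS. The swelling inputs come from a 0–3 scale, not the VAS or calipers. If swelling is less well powered than those inputs imply, Holm recovers less. The direction does not depend on any of this, because Holm is never less powerful than Bonferroni.

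The article does not establish that both endpoints are required, nor that the correction is needless. It leaves open which rule applies, and results exist on which the two rules disagree.

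**What to change.** If separate claims are intended, replace the Bonferroni sentence in Statistical analysis with: *The primary endpoints will be tested by Holm's step-down procedure at a family-wise 5% level; efficacy is claimed separately for each endpoint rejected, and relief of both pain and swelling is claimed only if both are rejected.* For two endpoints, the smaller p value is compared with 0.025 and, if significant, the larger with 0.05. For a larger family, the steps follow the number of primary variables, so that number should be stated.

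If the sponsor intends that both must succeed, say so and test each at the full 0.05 with no correction. Holm would then be too strict: p = 0.03 and p = 0.04 pass a both-required rule, but Holm rejects neither.

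The change needs no extra patients or data. Holm's simultaneous confidence intervals are less simple than Bonferroni's. Recruitment is under way, so the change needs an amendment before unblinding, which under the Ethics section goes to each centre's ethics committee and to the registry.

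### The sample size spends the full 5% on each primary outcome although Bonferroni is planned, and 82 per group matches only an undeclared one-sided test, so the stated 90% power for pain does not hold at 82 evaluable per group

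*Protocol article*

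**What the plan says.** In Sample size estimation the article says: "This study includes two primary outcomes: joint pain and joint swelling". Each outcome is sized separately, "On the basis of a 5% type I error rate" and with 90% power. For pain the inputs are "47% participants in treatment group (Qingpeng ointment plus diclofenac sodium tablets) had significant relief of joint pain" and "25% participants in control group (diclofenac sodium tablets) had significant relief of joint pain", and the result is that "the sample size of each group was 82". Dropout is then added: "Assuming a 20% dropout rate, a total of 206 participants should be recruited, with 103 participants in each group". Swelling is sized from means of 0.45 and 0.87 (SD 0.37 and 0.64) on a 0–3 scale, giving 27 per group. The larger number is adopted.

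Statistical analysis sets the threshold, "with a statistical significance of *p* value less than 0.05", and then adds: "For the co-primary endpoints, Bonferroni correction will be performed to correct multiplicity". It gives no divisor. Primary outcomes are analysed by intention to treat, with LOCF for dropouts. Neither section says whether tests are one- or two-sided.

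The number of primary tests is also open. Sample size estimation counts two outcomes. Primary outcomes lists four measures: pain VAS, swelling VAS, joint width and joint thickness.

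**The concern.** Bonferroni tests each endpoint at 0.05 divided by the number of endpoints. Neither sample size calculation makes that division, so the level used for sizing is not the level planned for testing. Taking the larger of two unadjusted sizes covers both outcomes at an undivided 5%, but leaves no allowance for a stricter test of pain, the outcome that sets the size.

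At stake is the chance of confirming an effect on pain if it is as large as assumed. A practical risk comes with it: if the divisor and the sidedness are still open when the data are unblinded, choosing them could decide whether pain is declared significant.

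**Working it through.** **Inputs** (Sample size estimation): p1 = 0.47, p2 = 0.25, difference 0.22, mean proportion 0.36; alpha 0.05; power 90%; dropout 20%. The sidedness is not stated, so both cases are shown. Normal quantiles: 1.645 (one-sided 0.05), 1.960 (two-sided 0.05), 1.282 (90% power).

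**1. Reproducing the plan's figures**

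Pain, n = 2 × 0.36 × 0.64 × (z_alpha + z_beta)² / 0.22²:
- One-sided: 0.4608 × 8.564 / 0.0484 = 81.5, rounded up to 82. This is the plan's figure.
- Two-sided: 0.4608 × 10.507 / 0.0484 = 100.0.

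Other standard formulas do not rescue the two-sided reading: pooled 98, unpooled 94.8, arcsine 97.8, continuity-corrected 107.

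Swelling, n = (0.37² + 0.64²) × (z_alpha + z_beta)² / 0.42²:
- One-sided: 0.5465 × 8.564 / 0.1764 = 26.5, rounded up to 27. This is the plan's figure.
- Two-sided: 32.6.

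Dropout: 82 / 0.8 = 102.5, rounded up to 103; 27 / 0.8 = 33.75, rounded up to 34. Both agree with the article. So 82 and 27 both follow from a one-sided 5% test.

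**2. Pain power at the level actually used**

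Power = Φ{[0.22√n − z_alpha √(2 × 0.36 × 0.64)] / √(0.47 × 0.53 + 0.25 × 0.75)}; the two square roots are 0.679 and 0.661. Example with n = 82, two-sided 0.025 (z = 2.241): (1.992 − 2.241 × 0.679) / 0.661 = 0.71, so power is 76.2%.

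| n per group | Sides | No correction (0.05) | Two tests (0.025) | Four tests (0.0125) |
|---|---|---|---|---|
| 82 | two | 84.2% | 76.2% | 67.3% |
| 82 | one | 90.7% | 84.2% | 76.2% |
| 103 | two | 91.4% | 85.9% | 79.2% |
| 103 | one | 95.4% | 91.4% | 85.9% |

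At 82 per group, moving from one- to two-sided costs about 6 points (90.7% to 84.2%). Bonferroni costs a further 8 points with two tests or 17 with four (84.2% to 76.2% or 67.3%). If the tests really are one-sided, Bonferroni alone takes 90.7% to 84.2% or 76.2%.

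**3. Size needed for 90% on pain** (pooled formula, then divided by 0.8)

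| Sides | Tests | Evaluable per group | Randomised per group | Total |
|---|---|---|---|---|
| two | none corrected | 98 | 123 | 246 |
| two | two | 116 | 145 | 290 |
| two | four | 134 | 168 | 336 |
| one | two | 98 | 123 | 246 |
| one | four | 116 | 145 | 290 |

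The planned total is 206.

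**4. Swelling.** At 82 per group, power on the stated inputs is 99.8% at two-sided 0.025 and 99.6% at 0.0125. The shortfall therefore falls on pain.

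**5. Holm with two endpoints, 82 per group.** Pain can be tested at 0.05 once swelling has passed at 0.025. Whatever the correlation, two-sided pain power is at least 0.842 + 0.998 − 1 = 0.840. One-sided, it is at least 0.907 + 0.999 − 1 = 0.906.

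**The case against.** Intention to treat with LOCF may bring all 103 per group into the analysis. One-sided with two tests, pain power is then 91% and there is no shortfall. This stands as an upper case. It requires that carried-forward values lose no information, whereas the article's own sizing relies on 82 evaluable. In the other three corrected cases at 103 per group, power is still 79% to 86%.

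It can also be said that none of these figures is the power of the planned test. The 47% and 25% are responder proportions on a self-developed scale, while the primary pain outcome is change in VAS, compared by a t test or a non-parametric test. That is correct. No VAS difference or SD is given, so the power of the planned comparison cannot be derived. The responder figures remain the only basis that the article gives for its 90%.

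A divisor of four is an assumption, since the article counts two outcomes and groups the swelling measures under one heading. That also stands, and it is why both cases are shown. Finally, if co-primary meant that both outcomes must succeed, no split of alpha would be needed; but then the Bonferroni sentence would have to go, so the text needs changing in either case.

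A reader might infer that the omitted Bonferroni step by itself takes pain power from 90% to 76% or 67%. The documents do not support that: two-sided, 82 per group never gave 90%, and about 6 points of the fall belong to the undeclared one-sided sizing.

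**Conclusion.** The point holds in this form: at the 82 evaluable per group on which the plan relies, the stated 90% for pain is not delivered once the promised correction is applied, under either sidedness. Two-sided, power is 84% before correction and 76% or 67% after it; one-sided, 91% before and 84% or 76% after. With all 103 per group and no loss of information it is 86% or 79% two-sided, and 91% or 86% one-sided. The first figure of each pair is for two tests, the second for four.

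These results assume 47% against 25%, a normal approximation and 1:1 allocation. Reading the threshold as two-sided is the usual convention, but it is an assumption here.

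A reader might also infer that the false-positive rate is inflated or that the trial is short of power overall. Neither follows. Bonferroni controls the family-wise error, and swelling stays above 99% on its stated inputs, so the chance of at least one primary success on those inputs is also above 99%. The defect is confined to the power claimed for pain and to the unstated divisor and sidedness.

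**What to change.** 1. State whether the primary tests are one- or two-sided, and list the primary tests by number (two or four). Do this before unblinding.
2. Restate the pain power at the level actually used, for 82 and for 103 per group, and say that it refers to a responder proportion.
3. Replace Bonferroni with Holm. It keeps the family-wise error at 5%, is never less powerful, and with two endpoints returns pain power to about 84% two-sided at 82 per group while keeping the swelling claim. With four tests the gain cannot be calculated, because the article gives no inputs for joint width and thickness.

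Holm does not restore 90% two-sided at 82 per group. Either the lower figure is accepted openly or more patients are needed; 98 evaluable (123 randomised) per group would be the size for a two-sided 0.05 test of pain. A fixed sequence with pain first is an option only: it also gives 84%, but no confirmatory swelling claim could be made if pain failed.

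The change itself is to wording in two sections. The article reports recruitment as under way, and under its Ethics section a revision goes to the ethics committee of each centre and to the registry, so the cost includes that amendment.

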### Quality control

Before the start of the study, the investigators will be trained, so that they will have a consistent understanding of the study protocol and can teach participants how to score the degree of joint pain, swelling, redness, and mobility and how to measure the width and thickness of affected joints. The investigators will also be trained how to fill in the case report form, and they should fill in the form truthfully and completely as required. The original examination report or its copy during the study should be pasted on the case report form. Special personnel will be set up in each center, who will be responsible for the management, distribution, and recovery of the study drugs. The drug distribution and recovery record form will be filled in when distributing and recovering the study drugs. Center for Evidence-Based Chinese Medicine, Beijing University of Chinese Medicine, as the coordinating center of this trial, will assign clinical research associates to regularly conduct monitors at each study center, to monitor whether the investigators comply with the study protocol and fill in the case report forms as required, and whether the data collected is accurate.

### Ethics

This study will be completed in accordance with the ethical principles in the Declaration of Helsinki and the Good Clinical Practice (GCP) Guideline. Beijing University of Chinese Medicine is the sponsor of this trial and will monitor and audit this project. The study has been approved by ethics committee of Fangshan Hospital, Beijing University of Chinese Medicine, ethics committee of the Second Affiliated Hospital of Zhejiang Chinese Medical University, and ethics committee of Liuzhou People’s Hospital. If the protocol needs to be amended, main investigators of this study will meet together to discuss, communicate, and draw conclusions on the revision. The revised protocol will be submitted to the ethics committee of each study center for approval, and an application for revision will also be submitted to the trial registry.

